### Implementation and evaluation of the programme

In the last two steps of the Intervention Mapping protocol, implementation and evaluation plans are developed.

Step 5: Implementation.

#### Selection of day-activity centres and participants

This study is conducted by a Dutch consortium of three large ID care provider services and the Intellectual Disability Medicine research group of the Erasmus Medical Centre at Rotterdam, in collaboration with the Centre of Human Movement Sciences of the University Medical Centre Groningen. HA-PAP is set in the three large ID care provider services, that include nineteen day-activity centres offering recreational activities to the target group. Two day-activity centres with reorganization problems or substantial personnel problems are excluded. Based on earlier research, we expect to obtain informed consent for about 50% of the participants [31]. Because we planned to conduct the intervention in groups of eight to ten seniors (see Paragraph: development of the programme), 7 day-activity centres with less than 15 seniors with mild or moderate ID are excluded. The ten remaining centres all have a large activity-room or a gymnasium facility in-house or nearby.

Our primary outcome measure is physical activity, defined as steps per day. We have data of seniors with a mild or moderate ID from the pilot of the study: “Healthy Ageing with Intellectual Disabilities” (HA-ID) [31] at our disposal (n = 37), in which we found a mean physical activity level of 5480 steps per day (SD 2146). With a power of 80% to detect a difference of 1073 steps (effect size 0.5) and a type I error of 0.10, 60 seniors in both the control group and the participation group are required. We assume a drop out of 20% and planned to start therefore with 80 seniors in each group.

Seniors had to be aged 45 years and over and to be able to participate in groups. Clients who were dependent on a wheelchair inside, who had dementia or had a medical contra-indication for participating in the physical activity programme would be excluded from the study. Managers of the selected ten day-activity centers provided anonymous information about their clients on date of birth, gender, level of intellectual disability, use of walking aid, presence of dementia and the ability to participate in group activities. Clients who satisfied the inclusion criteria are selected (n = 237). Clients who are competent according to their behavioral therapist, will be informed about the project by the staff members who are familiar to them. The information will be structured using specific Patient Information Forms and subsequently written informed consent will be obtained. If older adults are not sufficiently competent to give informed consent themselves, Patient Information Forms and informed consent forms will be sent by mail to their legal representatives. Informed consent for blood sampling will be obtained separately and is no precondition for participation.

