#### Randomization

To help ensure comparability of the participants conducting the programme and the seniors in the control group, we looked for the best possible match with respect to sex, age, intellectual disability, the use of a walking aid and provider service. The matching procedure was conducted with the data of the potential 237 participants (see previous Paragraph) using chi-square and t-tests. The best match was found when the ten day-activity centers were divided into two specific groups of five centres each. We subsequently checked the comparability of important day-activity centres’ characteristics in both groups, that is the availability of a gymnasium nearby and involvement of a physical-activity instructor in the day-activity centres’ activities. These characteristics appeared to be comparable. The chairman of the steering group, in presence of the researcher and a senior staff member Public Relations, randomly selected one of the two groups of five day-activity centers who will conduct the programme. The remaining group of five day-activity centres will serve as the control group. Because the implementation of the programme has to be prepared and organized, the sequence is only concealed for the clients and family, not to the day-activity centres’ managers. After the informed consent procedure has ended, all participants and/or their family will receive a confirmation of participation in the study and information about the intervention allocation.

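### The plan's own figures (237 eligible clients, about 50% consent) give about 118 starters, not the planned 160, and about 47 finishers per arm against the 60 required

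*Protocol article*

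**What the plan says.** All the figures stand in the article's Step 5, under *Selection of day-activity centres and participants* and *Randomization*.

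- **Required size:** "60 seniors in both the control group and the participation group are required". The inputs given for this are 80% power, a target difference of 1073 steps (half a standard deviation), alpha 0.10, and a standard deviation of 2146 steps from a pilot sample of 37.
- **Planned start:** "We assume a drop out of 20% and planned to start therefore with 80 seniors in each group".
- **Expected consent:** "we expect to obtain informed consent for about 50% of the participants". The sentence after it sets the minimum centre size: "7 day-activity centres with less than 15 seniors with mild or moderate ID are excluded".
- **Available pool:** of nineteen centres, two are excluded for organisational or staffing problems and seven for size, which leaves ten. In those ten, "Clients who satisfied the inclusion criteria are selected (n = 237").
- **Timing:** consent is described after this selection and in the future tense. Under *Randomization* the same people are still only potential participants: "The matching procedure was conducted with the data of the potential 237 participants".

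**The concern.** The 237 is a count before consent, and the pool is closed. All ten remaining centres are allocated, five to each arm, and the article names no other source of recruits and no higher consent rate. The 50% is a working input, since it is given just before the minimum centre size is set. Applied to the 237, it cannot produce 160 starters.

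If so, the sample size in the article is out of reach under the article's own assumptions. A reader would credit the trial with more precision than its recruitment plan supports.

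**Working it through.** **1. The plan's own figures.** With a difference of 1073 and SD 2146, d = 1073/2146 = 0.5. The article does not say whether alpha is one- or two-sided; two-sided is assumed here.

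n per arm = 2 × (1.645 + 0.842)² / 0.5² = 49.5, so 50, or 51 with the t distribution.

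The stated 60 therefore does not reproduce. One-sided alpha 0.10 gives 37. Nor does the start of 80: 60/(1 − 0.20) = 75, and 80 × 0.80 = 64. The comparison below uses 60 because that is the number the article calls required.

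**2. Recruitment yield** (inputs 237, 50% and 20%, all from the article; the equal split is an assumption)

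| Step | Arithmetic | Result | Article |
|---|---|---|---|
| Starters, total | 237 × 0.50 | 118.5 | 160 |
| Starters per arm | 118.5 / 2 | about 59 | 80 |
| Finishers, total | 118.5 × 0.80 | 94.8 | 120 required |
| Finishers per arm | 94.8 / 2 | 47.4 | 60 required |

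Starters fall 26% short (41.5/160) and finishers 21% short (12.6/60). Even with no drop-out, 59 per arm is just under 60.

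**3. Consent rate that would be needed**

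- 160 starters: 160/237 = 67.5%.
- 60 finishers per arm: 120/0.80 = 150 starters; 150/237 = 63.3%.
- The 50 to 51 finishers per arm that the stated inputs call for: 125/237 to 127.5/237, or 53% to 54%.

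The yield at nearby rates, as 237 × rate × 0.80 / 2: 45% gives 43 finishers per arm, 50% gives 47, 55% gives 52, 60% gives 57.

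**4. Power without clustering** (two-sample t test, d = 0.5, two-sided alpha 0.10)

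Noncentrality = 0.5 × √(n/2). At n = 47.4 it is 2.43 and power is 78%. At n = 60 it is 2.74 and power is 86%.

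**5. Power with clustering.** The article plans generalized estimating equations that correct for centre, but gives no intracluster correlation (ICC). The values below are assumptions shown as a range. With five centres per arm, m = n/5, design effect = 1 + (m − 1) × ICC, noncentrality = 0.5 × √(n / (2 × design effect)), referred to t with 8 degrees of freedom at two-sided alpha 0.10, before any gain from baseline adjustment.

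| Assumed ICC | Design effect at 47.4 / 60 | Power at 47.4 | Power at 60 | Points lost to the shortfall |
|---|---|---|---|---|
| 0.01 | 1.08 / 1.11 | 68.8% | 76.6% | 7.9 |
| 0.05 | 1.42 / 1.55 | 58.7% | 64.2% | 5.5 |
| 0.10 | 1.85 / 2.10 | 49.7% | 53.3% | 3.6 |

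Lost points are taken from unrounded powers.

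**6. Detectable difference at 80% power, same model.** Here it is 2146 × 2.727 × √(2 × design effect / n), where 2.727 is the noncentrality giving 80% power on 8 degrees of freedom. At 47.4 per arm this is about 1252, 1434 and 1634 steps for ICC 0.01, 0.05 and 0.10, against 1126, 1330 and 1548 at 60. The planned difference is 1073.

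**The case against.** The best defence is that the gap does little harm on the plan's own terms. The stated inputs need only 50 to 51 per arm, so 47 leaves power about two points under 80%. The consent figure is approximate, and 55% would give 52 finishers per arm. The 50% is also used explicitly only to screen out small centres.

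Much of this stands, and it sets the size of the point. It does not remove the contradiction. The article calls 60 required and plans 80; reaching those numbers takes 63% to 68% consent, more than an approximate 50% can cover. Any margin of 60 over 51 is also the only room the calculation leaves for clustering, and the shortfall uses it up.

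Three stronger readings are tempting, and the documents do not support them.

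- *Only 40 to 50 seniors can receive the programme.* A reader might infer this from five centres and groups of eight to ten. Nothing in the article limits a centre to one group, and the 15-senior rule is a minimum. The ten centres average 23.7 eligible clients, so 50% consent gives about 12 per centre.
- *Recruitment is what takes power down to 50% to 69%.* Most of that fall would occur at 60 per arm as well, because the calculation makes no allowance for centres.
- *The trial enrolled too few.* The article reports no enrolment. This is an inconsistency in planning only.

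**Conclusion.** The point holds as an internal contradiction. Under the article's pool, consent rate and drop-out, expect about 118 starters and 95 finishers, not 160 and at least 120. The totals rest only on figures in the article. The per-arm figures of about 59 and 47 assume an equal split, which is not assured: whole centres are allocated, and no eligible count per group of centres is given.

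Attributable to recruitment alone, the loss is about 8 points of power without clustering (86% to 78%), and about 8, 5.5 and 4 points at assumed ICCs of 0.01, 0.05 and 0.10. The further loss from ignoring clustering, and the failure of 60 and 80 to reproduce, are separate faults in the same calculation. Severity: should-fix. The analysis method and the validity of its inference are not affected.

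**What to change.** Change the sample size paragraph in one of two ways.

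1. Keep the 50% and restate the expected size as about 59 starters and 47 finishers per arm. Give the power or detectable difference at that size, allowing for clustering by centre, with the ICC labelled as an assumption and shown as a range.
2. Keep 80 starters per arm, replace the 50% by the 67.5% consent that this requires, and say why that rate is realistic.

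In either case, state whether alpha is one- or two-sided and show how the required number and its inflation for drop-out were obtained. The cost is a rewritten paragraph. Under the first option the stated power becomes less favourable; under the second the higher consent rate has to be defended. Neither changes the design or the data collection.

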## Methods and design

This study will evaluate the efficacy of the “Healthy Ageing- Physical Activity Programme (HA-PAP) for seniors with Intellectual Disabilities”. More specifically, physical activity, fitness and health indices will be compared between older adults with mild-moderate intellectual disabilities (ID) who are assigned to the HA-PAP and who will be given usual care. The programme is developed to be executed in day-activity centres of care organisations for people with ID in the Netherlands, in groups of eight to ten seniors. Intervention Mapping (IM) was applied to systematically develop the programme [12]. The efficacy of the programme will be evaluated in a cluster-randomized clinical trial and to minimize contamination, the level of day centres is used as the randomization level.

HA-PAP was approved by the Medical Ethics Committee of the Erasmus University Centre Rotterdam (NL 29573.078.09).

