#### Analysis

Generalized estimation equations will be used to identify significant differences in the primary and secondary outcome measures between participants and controls, correcting for day-activity centre as cluster. The outcomes at the end of the intervention for the control group and participation group will be compared, adjusted for outcome differences at baseline.

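### The stated 80% power with 60 seniors per arm is not established for a trial that allocates five day-activity centres to each arm

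*Protocol article*

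**What the plan says.** In the Protocol article, the section on selection of day-activity centres and participants takes a pilot SD of 2146 steps per day (n = 37) and states: "With a power of 80% to detect a difference of 1073 steps (effect size 0.5) and a type I error of 0.10, 60 seniors" per group are required. It continues: "We assume a drop out of 20% and planned to start therefore with 80 seniors in each group". No other input to the calculation is given.

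The design and the analysis work at a different level. Methods and design says that "the level of day centres is used as the randomization level". Randomization explains that the ten centres were first divided into two matched sets, after which the chairman of the steering group "randomly selected one of the two groups of five day-activity centers who will conduct the programme". Analysis plans generalized estimating equations "correcting for day-activity centre as cluster", with end-of-intervention outcomes adjusted for baseline differences.

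**The concern.** The power statement describes a comparison of independent seniors. The trial compares two sets of five centres. Seniors in one centre share staff, instructors, a group programme and a provider service, so their step counts may be correlated. Any such correlation lowers the information per senior, and with five centres per arm the number of centres limits the precision more than the number of seniors does.

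At stake is how a null result is read. If 80% power for 1073 steps is taken at face value, a non-significant result will look like fair evidence against a difference of that size. Whether the design supports that reading cannot be judged from the figures given.

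**Working it through.** **Inputs from the Protocol article.** Difference 1073, SD 2146 (1073/2146 = 0.5), alpha 0.10, power 80%, 60 per arm required, 20% dropout, 80 per arm enrolled, five centres per arm, baseline-adjusted analysis by centre.

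**Assumptions (not in the article).** Two-sided test; ICC 0.01 to 0.10; equal centre sizes; baseline correlation r of 0, 0.4 or 0.6, acting equally within and between centres; and, as a small-sample reference, t with 10 − 2 = 8 degrees of freedom.

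**Step 1: the plan's own figure.** For independent seniors, n per arm = 2(1.645 + 0.842)² / 0.5² = 49.5, so 50. One-sided 0.10 gives 37 and two-sided 0.05 gives 63. None of these is 60. With 60 independent seniors per arm, power is Φ(0.5 × √(60/2) − 1.645) = Φ(1.094), about 86%.

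**Step 2: could the surplus be a clustering allowance?** 60/50 = 1.2. With 60/5 = 12 per centre, the design effect is 1 + 11 × ICC. Setting this to 1.2 gives ICC = 0.2/11 = 0.018. Without rounding to 50, power by normal approximation falls below 80% at an ICC of about 0.019. The surplus would therefore cover an ICC of about 0.02 and no more.

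**Step 3: power for five versus five centres.** With m completers per centre, the variance of the standardised difference is V = 2(1 − r²)[1 + (m − 1)ICC] / (5m), and the noncentrality is 0.5/√V. Example with m = 12, ICC 0.05, r = 0: design effect 1.55; V = 2 × 1.55/60 = 0.0517; noncentrality 2.20. The normal approximation gives Φ(2.20 − 1.645), about 71%. Noncentral t with 8 df (critical value 1.860) gives 64%.

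With 60 per arm and two-sided alpha 0.10:

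| | ICC 0.01 | 0.02 | 0.05 | 0.10 |
|---|---|---|---|---|
| Design effect | 1.11 | 1.22 | 1.55 | 2.10 |
| Power, unadjusted, normal | 83% | 80% | 71% | 60% |
| Power, unadjusted, t 8 df | 77% | 73% | 64% | 53% |
| Power, r = 0.4, t 8 df | 83% | 79% | 71% | 59% |
| Power, r = 0.6, t 8 df | 91% | 88% | 81% | 70% |
| Steps detectable at 80%, unadjusted, t | 1126 | 1180 | 1330 | 1548 |
| Steps detectable at 80%, r = 0.6, t | 900 | 944 | 1064 | 1239 |

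**Step 4: completers.** The enrolled number does not match the required one: 60/0.8 = 75, not 80, while 80 × 0.8 = 64. Taking the planned 80 as given, there are 64 completers per arm, or 12.8 per centre. Unadjusted power is then 85/82/73/61% (normal) or 79/75/66/54% (t). This is a gain of one to two points and does not change the picture.

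**The case against.** The strongest reply is that the headline loss belongs to an analysis the trial does not plan. The Analysis section fixes a baseline-adjusted comparison. If baseline and follow-up step counts correlate at 0.6, power meets 80% at every ICC in the table except 0.10. This stands, and it means that a reader who infers that the stated power is overstated, or that the trial is underpowered, goes further than the article allows. It gives neither an ICC nor a baseline correlation, and the answer turns on both.

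Second, the 8 degrees of freedom are an assumption of this check. The article names only GEE with centre as cluster, and the reference distribution may be fixed in a document not shown. This also stands, so both versions are given. A small-sample reference is the prudent choice with ten clusters.

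Third, a reader might infer that 60 is simply the individually randomised answer and that clustering was overlooked. The text does not support that either. The stated inputs give 50, the origin of 60 is not explained, and a factor of 1.2 fits a small clustering allowance as well as a dropout inflation (50 × 1.2 = 60). For the same reason it cannot be credited as a clustering allowance.

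Finally, an article condenses. But this one states a calculation with its inputs and result, and the objection is that the result does not follow for the design described. It is not a complaint about missing detail.

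**Conclusion.** The point holds as a failure of justification: 80% power for 1073 steps is not established for five versus five centres. The stated inputs do not reproduce 60 per arm, and the unexplained surplus would absorb an ICC of only about 0.02 by normal approximation. On the assumptions above, power at 60 per arm runs from 53% (ICC 0.10, no adjustment, t) to 91% (ICC 0.01, r = 0.6, t). At a moderate ICC of 0.05 it is 64% unadjusted, 71% with r = 0.4 and 81% with r = 0.6. A shortfall is likely there unless baseline correlation is strong, but it is not certain.

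The calculation treats the ten centres as independently allocated units. Allocation was in fact one draw between two pre-formed sets, so the 8 df version is itself an approximation. The planned analysis, which already accounts for centre, is not faulted.

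**What to change.** Replace the power statement with a cluster-trial calculation that gives:

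- five centres per arm and the expected completers per centre (64 per arm, about 12.8 per centre, after 20% dropout from 80);
- an ICC range, with its source or stated as an assumption;
- the sidedness of the 0.10 test and a small-sample reference distribution suited to ten centres;
- the baseline correlation assumed for the planned adjustment;
- the resulting power for 1073 steps, or the difference detectable at 80% power.

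The same paragraph should explain how 60 was reached and reconcile 60 with 80.

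The cost is one rewritten paragraph, and the stated power may become less favourable. The change restates the figure and does not guarantee 80%. Without baseline adjustment and by normal approximation, holding five centres per arm, an ICC of 0.05 would need 50 × 0.95 / (1 − 50 × 0.05/5) = 95 completers per arm. At an ICC of 0.10 the denominator is zero, so no centre size would be enough.

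### The sample-size figures do not follow from the stated inputs: effect size 0.5, 80% power and a type I error of 0.10 do not give 60 per group, and 60 with 20% drop-out does not give 80.

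*Protocol article*

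**What the plan says.** The calculation is in the protocol article, under Selection of day-activity centres and participants. The variability comes from a pilot of 37 seniors, with "a mean physical activity level of 5480 steps per day (SD 2146"). The targets are given as "With a power of 80% to detect a difference of 1073 steps (effect size 0.5") and "a type I error of 0.10". Whether the test is one- or two-sided is not said. The result is that "60 seniors in both the control group and the participation group are required". The next sentence makes the starting number a consequence of drop-out: "We assume a drop out of 20% and planned to start therefore with 80 seniors in each group".

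No intracluster correlation or design effect enters this calculation. Clustering appears in the Analysis section, where generalized estimating equations are to be used, "correcting for day-activity centre as cluster". That section names no significance level, so the sample-size paragraph is the only place in the article that gives one.

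**The concern.** The paragraph prints its inputs and its outputs, so a reader can repeat the calculation, and it fails at both steps. The number required does not match the effect size, power and type I error. The number to start with does not match the number required and the drop-out rate. This is not a detail that a journal article has left to a fuller document; it is a disagreement among figures that the article itself prints.

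At stake is what the trial was sized to do. The only stated type I error sits inside a calculation that does not reproduce at that level. A reader therefore cannot tell which of the printed values the sponsor relied on: the level, the power, the drop-out rate or the size.

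**Working it through.** **Inputs**, all from Selection of day-activity centres and participants:
- SD 2146 and difference 1073, so d = 1073/2146 = 0.500, which agrees with the stated effect size
- power 0.80
- type I error 0.10, sidedness not stated
- equal groups, 60 required per group
- drop-out 20%, 80 to start per group

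**Step 1: the number required.** The normal approximation for two means is n per group = 2(z_alpha + z_power)²/d², with z for 80% power = 0.842 and d² = 0.25. The t-test value is the exact noncentral-t solution for the same inputs.

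| Test | Normal approximation | Noncentral t | Per group (t) |
|---|---|---|---|
| Two-sided 0.10 | 2(1.645 + 0.842)²/0.25 = 49.5 | 50.1 | 51 |
| One-sided 0.10 | 2(1.282 + 0.842)²/0.25 = 36.1 | 36.5 | 37 |
| Two-sided 0.05 (not stated; for comparison) | 2(1.960 + 0.842)²/0.25 = 62.8 | 63.8 | 64 |

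The stated 60 is not reproduced by either reading of 0.10, nor by two-sided 0.05.

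**Step 2: the power that 60 per group gives (t-test, d = 0.5).**
- two-sided 0.10: 86%
- one-sided 0.10: 93%
- two-sided 0.05: 77.5%

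None of these is the stated 80%.

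**Step 3: the drop-out step.** The standard inflation is n/(1 − drop-out).
- 60/(1 − 0.20) = 75, not 80
- the cruder form, 60 × 1.20 = 72, is not 80 either
- the drop-out that takes 80 to 60 is 1 − 60/80 = 25%
- 80 starters with 20% drop-out leave 80 × 0.80 = 64, not 60

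This step uses only the printed 60, 20% and 80, so it does not depend on any choice of test.

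**Step 4: both steps from the stated inputs (t-test).**
- two-sided 0.10: 51 completers, 51/0.8 = 63.75, so 64 starters
- one-sided 0.10: 37 completers, 37/0.8 = 46.25, so 47 starters

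**Step 5: which single changes would give the printed numbers?**

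Routes to 80:
- two-sided 0.05 at 80% power: 64/0.8 = 80 by the t-test (63/0.8 = 78.75, so 79, by the normal approximation)
- two-sided 0.10 at about 88% power: 64 completers, 64/0.8 = 80
- two-sided 0.10 at 80% power with drop-out applied twice: 51/0.64 = 79.7

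Routes to 60, or close to it:
- two-sided 0.10 at 85% power: 58 (normal) or 59 (t)
- 50 × 1.2 = 60, that is, a 20% allowance for drop-out or clustering already included

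Several routes lead to each figure. None gives 60 and 80 together with a single 20% drop-out step, because Step 3 rules that out.

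**The case against.** The strongest defence is that the printed sizes err on the safe side. At two-sided 0.10 the individual-level need is 51 completers and 64 starters, and 60 and 80 exceed both. With 80 starters and 20% loss, 64 remain, which covers the stated 60. The surplus might be a deliberate margin. It could be an allowance for clustering, or 75 rounded up to whole programme groups: the groups hold eight to ten seniors, and ten groups of eight make 80. That much stands. The mismatch alone does not show an underpowered trial, and a reader who inferred underpowering from it would go beyond the document.

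The defence does not remove the inconsistency. The article mentions no margin, design effect or rounding. It presents 60 as the result of effect size, power and type I error, and 80 as the result of 20% drop-out. Even if 60 held a hidden allowance, 60 to 80 would still not be a 20% loss.

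A reader might also infer the opposite: that 0.10 is a slip for 0.05, since two-sided 0.05 gives 64 and 80. The documents do not support this as a conclusion. No passage states 0.05, the match to 80 holds for the t-test but not for the normal approximation (79), and that level leaves 60 unexplained. Other changes to the inputs reach 80 as well.

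**Conclusion.** The sample-size paragraph is wrong as written, in two independent places. From its own inputs the number required per group is 51 two-sided or 37 one-sided, against a printed 60. From its own 60 and 20%, the starting number is 75, against a printed 80. At 60 per group the power is about 86% at two-sided 0.10, not 80%.

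Which item is misstated cannot be settled from the article. It could be the type I error, the power, the drop-out rate, or a size that includes an unreported allowance. The finding is that the figures disagree, not that the trial has too few participants or that a different level was intended.

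These results assume a comparison of two independent means with equal groups, the stated SD, and no clustering. Any loss of power from randomising ten centres comes on top and is a separate question.

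**What to change.** State the type I error for the primary test and whether it is one- or two-sided, say which printed input or size is wrong, and restate the figures so that they agree. Use one method throughout. By the t-test at d = 0.5, 80% power and 20% drop-out, the consistent pairs are:
- two-sided 0.10: 51 completers and 64 starters per group
- two-sided 0.05: 64 completers and 80 starters per group

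Alternatively, keep 80 starters, correct the completers to 64, and restate the power: about 88% at two-sided 0.10, or 80% at two-sided 0.05. If 60 or 80 already includes an allowance for clustering or group size, state that allowance and its value.

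The choice of level is the sponsor's design decision and should not be made just because it matches one of the two printed numbers. Whichever is chosen, account for clustering by centre as a separate, stated step.

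The cost is one or two corrected sentences. The planned enrolment of 80 per group need not change for the arithmetic to be put right.
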